### Confidentiality {27}

The trial staff will ensure that the participants’ anonymity is maintained. The participants will be identified only by a participant ID number on all trial documents and any electronic database. Carers will have the same participant ID number as the participant with AD, followed by the word ‘CARER’. All documents will be stored securely and only accessible by trial staff and authorised personnel. The trial will comply with the Data Protection Act, which requires data to be anonymised as soon as it is practical to do so.

All data captured in the ILiAD study will be kept for 5 years after the end of the study whereupon it will be destroyed according to University of Oxford standard disposal procedures

### Plans for collection, laboratory evaluation and storage of biological specimens for genetic or molecular analysis in this trial/future use {33}

The only laboratory tests performed are blood tests at screening. The samples will be analysed by standard methods in clinical laboratories. Samples will be considered a gift to the study and destroyed after analysis according to standard NHS disposal methods. There is therefore no planned storage of biological materials for use in the current trial or in future studies.

## Statistical methods

### Statistical methods for primary and secondary outcomes {20a}

A trial-specific statistician based at the Centre for Statistics in Medicine, University of Oxford, will perform statistical analysis.

As the trial is crossover in design, all analyses will be within participants, comparing outcome measures after taking the placebo and after taking levetiracetam. Thus, the analyses of the primary and secondary outcomes relating to cognition, behaviour and quality of life will be based on the differences between the observations at the efficacy visits (week 8 and week 20) of the levetiracetam and placebo periods.

Within a given patient, levetiracetam and placebo will be compared using the paired t-test and the analysis of covariance adjusting for baseline values. We will compare results at 8 weeks to the initial baseline testing and at 20 weeks to the further baseline testing at 12 weeks. All results will be presented with 95% confidence intervals. For each carer who has consented to provide data, quality of life measures will likewise be compared between the observations at the week 8 and week 20 visits. Appropriate sensitivity analyses will be performed to confirm the robustness of the data.

EEG will be computationally analysed, after standard cleaning, downsampling and artefact rejection. Typical EEG data features of interest include time series measures (for example, mean, variance, skewness, kurtosis and coastline), frequency based features (e.g. band-passed power and rhythmicity) and channel pair-wise bivariate connectivity metrics. These baseline EEG features will be correlated with clinical outcome measures.

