### Trial design {8}

ILiAD is a randomised double-blind placebo-controlled crossover study to evaluate whether treatment with levetiracetam is superior to placebo in its effect on memory function in people with AD. The study is counterbalanced and participants either receive placebo or levetiracetam first. Data are compared, for a given individual, from when the participant is taking levetiracetam to when taking placebo. Given the overall short duration of the study, it is not anticipated that there will be marked progression of the dementia during the study.

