### Subsequent visits

There will be safety checks at week 2, week 4, week 14, and week 16. These timepoints coincide with patients receiving levetiracetam 250 mg twice daily or 500 mg twice daily. Should they so wish, some of the visits may be at the patient’s home or remotely by telephone. If any visits are at the patient’s home, then the carer must also be present throughout that visit. If the visit is conducted remotely by telephone, the researcher should complete all assessments that are possible to complete by telephone as per the schedule of assessments.

At weeks 8 and 20, patients and carers will be required to attend the clinical research site for detailed assessments including all of the measures of efficacy performed at baseline as well as detailed reporting of potential side effects. In the event that visits cannot be conducted at the clinical research site, the visits can be conducted remotely by telephone. The visits should still be conducted as per the schedule of assessments and by staff delegated to complete the specified study tasks. Any assessments not completed need to be documented as a protocol deviation. At week 24, there will be a further telephone consultation with patients who have completed the trial.

In brief the visits can be summarised as follows:

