### Sample size {14}

The trial is relatively short and one would not anticipate being able to detect changes in ADAS-Cog over this time-frame. Therefore, the trial is powered to detect a standardised effect of 0.7 in a specific and sensitive test of hippocampal function that has already been tested in people with AD [24, 25]. The estimated variability of 2% was taken from data on a memory-binding task for older individuals (aged 60–83) [26]. The standard deviation of the difference between the treatment and placebo was then calculated assuming equal variability in the two groups. This yielded an estimate of 3%. Using the two-sided test for paired means in PASS 11, the total sample required to detect a mean difference of 2.1% with a standard deviation of the difference of 3% and achieve 90% power at a 5% significance level in 24 patients.

Therefore, a sample size of 30 allows an attrition rate of 20% for the study still to be able to detect a meaningful difference in sensitive measures of cognitive function.

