## Assignment of interventions: allocation

### Sequence generation {16a}

As ILiAD is a crossover trial, patients will be randomised 1:1 levetiracetam: placebo. All tablets of levetiracetam and placebo will appear identical. Restricted block randomisation will be performed by the Centre for Statistics in Medicine, University of Oxford, who will generate a series of randomisation codes. The investigators and patients will be blinded to treatment allocation.

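### The stated paired t-test and baseline-only ANCOVA contain no period term, so any period effect would cost power and, if completers are unequal by sequence, bias the estimate.

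*Protocol article*

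**What the plan says.** Section {20a} of the protocol article states that "levetiracetam and placebo will be compared using the paired t-test and the analysis of covariance adjusting for baseline values". The only covariate named is baseline. The sensitivity analyses mentioned there are not specified, and no section names a period or sequence effect.

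The sample size section {14} rests on the same test: "Using the two-sided test for paired means in PASS 11", with "the total sample required to detect a mean difference of 2.1% with a standard deviation of the difference of 3" per cent, to "achieve 90% power at a 5% significance level in 24 patients". It adds that "a sample size of 30 allows an attrition rate of 20" per cent. Allocation is by restricted blocks ({16a}: "patients will be randomised 1:1 levetiracetam: placebo"), with 15 participants planned per sequence.

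Two descriptions of the analysed quantity stand side by side. Outcomes {12} defines the primary outcome as change within each arm from that arm's own starting value, and {20a} repeats this (week 8 against week 0, week 20 against week 12). Section {20a} also bases the analyses on differences between the week 8 and week 20 observations.

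On time trends, Trial design {8} says only that "it is not anticipated that there will be marked progression of the dementia during the study". The visit list justifies the week 12 retest by carry-over, not by practice.

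**The concern.** In a two-period crossover each participant's levetiracetam-minus-placebo difference contains the treatment effect plus or minus any difference between the periods. The sign depends on which treatment came first. A paired t-test pools all these differences as if they shared one mean. Two things follow if the periods differ:

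- With equal sequences the shift cancels from the mean but stays in the estimated variance. The test becomes conservative and loses power.
- With unequal sequences among those analysed, part of the shift is read as a drug effect, in either direction.

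A period difference is credible because the same memory task is given four times. The remark on disease progression does not deal with practice. Equal sequences at analysis are not secured either: 20% attrition is planned, {11b} collects no data after exit, and the Discussion says that completers will be analysed preferentially. The trial is meant to inform whether a larger study follows, so a real effect missed for this reason would matter.

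**Working it through.** **Inputs.** From {14}: mean difference 2.1, SD of the within-participant difference 3, two-sided 5% level, 24 completers from 30 recruited. From the intervention description: 15 per sequence. The period shift π (period 2 minus period 1 in the analysed quantity) is not in the documents. It is assumed at 0, 1, 2 and 3 points. The SD of 3 is applied to whichever difference is analysed.

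**The plan's own figure.** For a paired t-test with n − 1 degrees of freedom and noncentrality (2.1/3)√n, power is 89.4% at n = 23 and 90.7% at n = 24. So 24 is reproduced, and 24/0.8 = 30.

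**Model.** Let τ be the treatment effect. The levetiracetam-minus-placebo difference has mean τ − π in the levetiracetam-first sequence and τ + π in the placebo-first sequence.

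- Paired t-test: pools all 24 differences, 23 degrees of freedom.
- Period-adjusted: average of the two sequence means, pooled within-sequence SD, 22 degrees of freedom.

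**Balanced completers, 12/12** (simulation). The mean of the differences is unbiased, but the variance that the paired test estimates rises from 9 to roughly 9 + π², for example 9 + 4 = 13 at π = 2.

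| π | Paired-t power | Power with period term | Paired-t rejection under the null |
|---|---|---|---|
| 0 | 91% | 91% | 5.0% |
| 1 | 89% | 91% | 4% |
| 2 | 82% | 91% | 2% |
| 3 | 68% | 91% | 0.6% |

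**Unequal completers.** Bias of the paired mean = π × (placebo-first count − levetiracetam-first count)/24. At 10 levetiracetam-first and 14 placebo-first the multiplier is 4/24 = 0.167:

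- π = 1: 0.17 points
- π = 2: 0.33 points (16% of 2.1)
- π = 3: 0.50 points (24% of 2.1)

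At 14/10 the sign reverses, and at π = 2 paired-t power is about 65%. The period-adjusted estimate has bias of about 0 and power of about 90% in both cases.

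**How likely is the imbalance?** If 6 of 30 (15/15) drop out unrelated to sequence, the split is hypergeometric with C(30,6) = 593,775 possible sets.

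- 12/12: C(15,3)² = 207,025, or 35%.
- 10/14 or worse, either way: 2 × [C(15,5) × 15 + C(15,6)] = 2 × (45,045 + 5,005) = 100,100, or 17%.
- 9/15, either way: 2 × 5,005 = 10,010, or 1.7%.

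**Price of the period term if there is no shift.** Power at 12/12 is 90.6% against 90.7%. At 10/14 it is about 90% against 91%.

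**The case against.** The strongest reply is that the primary outcome is corrected by each period's own baseline. Practice carried to week 12 then cancels, and only a difference between the week 0–8 and week 12–20 gains is left. This stands, and it may make the relevant π much smaller than the raw week 8 to week 20 learning. It does not dispose of the point. Learning could plausibly be larger early on, and the week 8 versus week 20 wording in {20a} leaves the full shift in place. Adjusting for baseline in the ANCOVA deals with period only indirectly.

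Second, no document gives a period effect for this task in this population, and at 1 point the balanced loss is only about 2 percentage points. This also stands. The larger losses need a shift close to the hoped-for drug effect.

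Third, large imbalance is unlikely by chance. A 9/15 split needs all six dropouts from one sequence. Both sequences receive levetiracetam, so intolerance does not obviously favour one, and nothing suggests that replacements would be allocated outside the blocks. The realistic case is therefore 10/14.

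Fourth, an unseen analysis plan may add a period term. It may, but the protocol names its tests, and these have none.

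A reader might also infer that moving visits to telephone ("the visits can be conducted remotely by telephone") shifts the primary outcome between periods. The documents do not support that. The primary outcome is a touchscreen task, and assessments that are not completed are to be documented as protocol deviations. A change of mode bears on the secondary scales only.

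**Conclusion.** The point holds as a conditional one: the stated analyses leave any period effect unmodelled, and a standard model would remove it at almost no cost. With balanced completers the consequence is lost power, from about 91% to 89, 82 or 68% at shifts of 1, 2 or 3 points. With 10/14 completers it is a bias of 0.17, 0.33 or 0.50 points, with the sign set by the direction of the imbalance and of the shift. These figures assume an SD of 3, 24 completers and a shift that the documents do not give.

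A reader might infer that the planned comparison is biased as designed, or that it raises the false-positive rate. The documents do not support this. With the planned 1:1 sequences the paired mean is unbiased, and a shift makes the test conservative. Nor can it be said that the trial will miss its 90% power, because that depends on an unknown shift. If dropout is unrelated to sequence, the bias averages out over repeated trials, but it remains in a single trial with unequal completers.

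**What to change.** Make the primary analysis a linear model with participant, treatment and period effects. For participants with both periods, this is equivalent to comparing the within-participant period differences between the two sequences. Apply it to the baseline-corrected primary outcome of {12}, and reconcile the week 8 versus week 20 wording in {20a} with that definition. Report the period effect with its 95% confidence interval. Keep the unadjusted paired t-test as a sensitivity analysis. Use the same model for the secondary scales, where a move to telephone could itself create a period difference.

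The cost is a change of wording and one degree of freedom. If there is no shift, power is essentially unchanged at 12/12 and about 90% at 10/14. The sample size stays at 24 completers from 30 recruited.

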### Interim analyses {21b}

No interim or additional analyses are planned as this is a small pilot study.

### Methods for additional analyses (e.g. subgroup analyses) {20b}

Subgroup analysis will be performed according to the EEG findings of participants and may also be performed for certain specific clinical parameters for example duration of disease.

### Methods in analysis to handle protocol non-adherence and any statistical methods to handle missing data {20c}

Missing data will be sought and supplemented where possible after consultation with the investigator. The control of the correctness of the data will be performed by central monitoring procedures. Unused data will be retained in the same way that used data is retained.

### Plans to give access to the full protocol, participant level-data and statistical code {31c}

On completion of the study, the entire protocol will be provided as an open access appendix to any arising manuscripts. Irretrievably anonymised datasets analysed during the current study are available from the corresponding author on reasonable request.

## Oversight and monitoring

### Composition of the coordinating centre and trial steering committee {5d}

The lead site is the John Radcliffe Hospital, Oxford University Hospitals NHS Foundation Trust. An annual report will be submitted to the Monitor who will also have access to all study data on request. The Oxford University Hospitals Trust / University of Oxford Trials Safety Group (TSG) will conduct a review of all SAEs for the trial reported during the quarter and cumulatively. The aims of this committee include:
To detect any trends, such as increases in un/expected events, and take appropriate actionTo seek additional advice or information from investigators where requiredTo evaluate the risk of the trial continuing and take appropriate action where necessary

### Composition of the data monitoring committee (DMC), its role and reporting structure {21a}

Given the short nature of the trial, the small number of planned participants and that the IMP is widely prescribed in clinical practice, it was agreed that a DMC was not required.

### Adverse event reporting and harms {22}

Levetiracetam, as outlined, is a well-tolerated and widely prescribed anti-seizure medication and is a drug of choice in older people with epilepsy. The safety and tolerability profile of levetiracetam is therefore very well-established and familiar to both investigators and General Practitioners. Common side effects from levetiracetam include asthenia, an effect on sleep and an effect on mood. Gastrointestinal disturbance, change in weight and rash are occasionally reported. The effect of levetiracetam on mood in patients with AD is captured within the data that will be collected from recruited participants. The full list of potential expected adverse events is listed in the Summary of Product Characteristics [33].

Given the familiarity with levetiracetam in both tertiary and primary care and, in particular, given that levetiracetam is being used at its licenced dose, non-serious adverse events will not be recorded within the ILiAD study unless they lead to withdrawal from treatment. Solicited and unsolicited adverse events are listed in Table 3 below:

**Table 3 Tab3:** Solicited and unsolicited potential adverse events associated with levetiracetam

Adverse event	Solicited	Unsolicited
**Asthenia**		x
**Change in weight**		x
**Cough**		x
**Effect on mood/behaviour**	x	
**Effect on sleep**		x
**Gastrointestinal disturbance**		x
**Nasopharyngitis**		x
**Rash**	x	

SAEs will be recorded from the time of taking informed consent to 28 days following the last administration of study medication. The participants in this study are from an older population and may have co-morbidities beyond Alzheimer’s disease. An event that is part of the natural course of the disease (i.e. disease progression or admission for standard treatment) will not be reported as an SAE. However, if the progression of the underlying disease is greater than that which would normally be expected, or if the investigator considers that there may be a causal relationship between the IMP or protocol design/procedures and the disease progression, then it must be reported.

Reportable SAEs will be reported on the SAE reporting form to the trial monitor within 24 h of the Site Study Team becoming aware of the event. The trial monitor will perform an initial check of the report, request any additional information, and ensure it is reviewed by the Medical Monitor on a weekly basis. It will also be reviewed at the next Trial Safety Group meeting. All SAE information must be recorded on an SAE form and emailed to CTRG. Additional and further requested information (follow-up or corrections to the original case) will be detailed on a new SAE Report Form and faxed/emailed to CTRG.

All SUSARs will be reported by the CI to the relevant Competent Authority and to the REC and other parties as applicable. For fatal and life-threatening SUSARS, this will be done no later than 7 calendar days after the Sponsor or delegate is first aware of the reaction. Any additional relevant information will be reported within 8 calendar days of the initial report. All other SUSARs will be reported within 15 calendar days. Treatment codes will be unblinded for specific participants.

Principal investigators will be informed of all SUSARs for the relevant IMP for all studies with the same Sponsor, whether or not the event occurred in the current trial.

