Screening visit: patient screened against inclusion/exclusion criteriaBaseline and randomisation visit: eligible patients who consent to participation are evaluated as outlined and randomised to either receive levetiracetam first or placebo first. Baseline data are captured as detailed in baseline assessmentsTelephone call 2 weeks after randomisation: as levetiracetam/placebo is uptitrating, there will be a telephone call at 2 weeks to ensure no adverse effects and document adherence4-week visit when participants in the active arm will have reached levetiracetam 500 mg twice daily.Eight week efficacy visit to evaluate effect of levetiracetam/placebo using all of the measures performed at the baseline visit.12-week crossover visit. Participants who were randomised to levetiracetam will have weaned to nil and start to take placebo and vice versa. Vital signs, adverse effects and adherence will be recorded. The cognitive and neuropsychiatric measures undertaken at baseline will be repeated to ensure no ‘carry over’ effect from patients who received levetiracetam initially.Telephone call 14 weeks after randomisation: as levetiracetam/placebo is uptitrating, there will be a telephone call at 2 weeks to ensure no adverse effects and document adherence16-week visit when participants in the active arm will have reached levetiracetam 500 mg twice daily.20-week efficacy visit (8 weeks after cross over visit) to evaluate effect of levetiracetam/placebo using all of the measures performed at the baseline visit.24-week end-of-study visit, 24 weeks post baseline. At this visit, patients will have weaned from either levetiracetam or placebo completely. Vital signs, medication adherence and adverse effects will be recorded.Telephone call at 28 weeks after randomisation, 4 weeks after weaning from study medication to document any adverse events from medication

Participants can also make unscheduled visits if required. These visits will be triggered by the participant at any stage through the trial should concerns, particularly relating to possible adverse effects, arise. If an unscheduled visit is required, dependent on the reason for the visit, the visit may occur at the clinical research site, at the participant’s home or telephonically.

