#### Secondary

Determination of side effects from levetiracetam in the study population compared to placebo. Anti-seizure medications are generally well-tolerated in people with epilepsy, but are not routinely administered to people who have not had a seizure. It is therefore clinically essential to determine if there are side effects in this patient group. This will be enquired about at each study contact.Determination of the effect on mood of levetiracetam in the study population compared to placebo using standardised scales such as Neuropsychiatry Index. Given that levetiracetam can have an adverse effect on mood, this will be specifically evaluated and monitored throughout. Principal comparisons will be between the start and end of each arm of the study.Determination of the effect on quality of life from levetiracetam in the study population compared to placebo using standardised scales such as the BADLS, EQ-5D and DSRS index (compare end of arm 1 to baseline and end of arm 2 to end of arm 1). Even were levetiracetam to not show an advantage on cognitive measures, were it to improve quality of life in people with AD that may make it a worthwhile treatment.Assessment and modelling of the EEG prior to starting levetiracetam and correlation with response to levetiracetam. It may well be that levetiracetam is not suitable for all people with AD. EEG could offer a simple non-invasive biomarker to better determine who may benefit from levetiracetam and similarly who may experience side effects. The EEG is performed at baseline and will be modelled and correlated with outcomes for each participant at study end.

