ILiAD is very different to most studies in AD. It is short, involves repurposing of an existing widely prescribed medication and, as a crossover study, all participants have the opportunity to be given levetiracetam. While AD generally progresses slowly, the hippocampal binding task we employ in this study offers a very precise assessment of memory function [24] and this test can detect changes that may be apparent over a few months. The test may therefore be helpful in other AD studies going forwards. Similarly, EEG may provide a very helpful non-invasive biomarker to determine who may benefit from specific treatments in AD. Future, longer duration studies will also help evaluate the possible enduring impact of levetiracetam on cognition in people with AD as well as monitoring for any adverse events. We appreciate that by choosing to preferentially analyse data from participants who complete the study, there might be a bias towards people who tolerate levetiracetam. To mitigate this we will record all adverse events and the reasons why participants may have had to withdraw from the study before completion. As this is, very much, a pilot study all such data will inform future work exploring the potential role of levetiracetam in those with dementia.

Perhaps most importantly, irrespective of results, ILiAD opens an entirely new frontier in the treatment of Alzheimer’s disease bringing together the fields of epileptology and cognitive neurology. Were an anti-seizure medication, not necessarily levetiracetam, shown to positively influence memory in AD, this would be revolutionary. Moreover, as the utility of anti-seizure medications is in neuronal network stabilisation, independent of the cause of perturbation to that neuronal network, it may be that anti-seizure medications will also prove beneficial in other dementing illnesses beyond AD.

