### Addendum: Adjustments owing to COVID-19 pandemic

At the time of initial submission, April 2020, owing to the coronavirus (COVID-19) pandemic, all ‘visits’ are now being performed telephonically to minimise any exposure of participants to hospital environments and to ensure that we do not burden NHS staff or facilities. IMP is delivered to the participant’s residence and there is no face-to-face contact between research personnel and participants. We are suspending all new recruitment to the study at the current time.

While we appreciate that these measures have a very significant impact on the trial, and if prolonged restrictions continue we may only be able to report safety data, we are nonetheless pleased that the study is being allowed to continue. Participants and their carers have invested considerably in the project and it would have been difficult had the trial stopped abruptly. Moreover, it remains important to complete research in populations who may be more vulnerable to COVID-19, but similarly are also more likely to have other health conditions that need addressment.

At the time of submitting the revised manuscript, ILiAD is planning on re-opening July 2021 with recruitment planned to end in July 2022. This is, though, contingent on how the COVID pandemic evolves over the next 18 months.

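### The rule against recording non-serious adverse events contradicts the outcomes, visit and discussion sections and, if followed, leaves much of the side-effect comparison with placebo without data

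*Protocol article*

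**What the plan says.** The rule stands in the protocol article under Adverse event reporting and harms {22}: "non-serious adverse events will not be recorded within the ILiAD study unless they lead to withdrawal from treatment". The reasons given are that clinicians know the drug well and that it is used at its licensed dose. Serious adverse events are recorded from consent until 28 days after the last dose, and the section adds that mood effects are captured in the data collected. Table 3 then marks mood/behaviour and rash as solicited, and the other listed events, including asthenia and effect on sleep, as unsolicited.

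Other sections say something different:

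- Outcomes {12}, Secondary, opens with "Determination of side effects from levetiracetam in the study population compared to placebo". It explains that these drugs are not normally given to people without seizures, concludes "It is therefore clinically essential to determine if there are side effects in this patient group", and adds "This will be enquired about at each study contact".
- Subsequent visits requires "detailed reporting of potential side effects" at weeks 8 and 20. It has adverse effects recorded at the week 12 crossover visit and again at week 24: "Vital signs, medication adherence and adverse effects will be recorded".
- The Discussion concedes that favouring completers may bias results towards people who tolerate the drug, and answers: "To mitigate this we will record all adverse events and the reasons why participants may have had to withdraw".

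**The concern.** Two opposite instructions stand side by side, and the one that withholds data is in the section that staff would consult on adverse events. An analysis plan cannot repair this later, because an event never entered cannot be analysed.

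The two rationales also pull apart. The harms section relies on familiarity with the drug, which comes mainly from people with epilepsy. The outcomes section treats the absence of such experience in people without seizures as the reason to measure side effects.

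Tolerability is a stated hypothesis and the first secondary objective. In the abstract's discussion it is one of the findings that could lead to a larger study. The COVID-19 addendum adds that "if prolonged restrictions continue we may only be able to report safety data". A short list of recorded events could then be taken as evidence of tolerability when it reflects only the recording rule. The described oversight might not reveal this: there is no data monitoring committee, the safety group's review is of serious events, and no audits are planned.

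**Working it through.** **1. Set the statements side by side.** The question is whether a non-serious event that does not cause withdrawal, such as mild asthenia, enters the trial record.

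- Harms {22}: no.
- Outcomes {12}: it is asked about at each contact and belongs to a placebo-controlled outcome, which implies yes.
- Subsequent visits, weeks 8 and 20: reported in detail.
- Subsequent visits, weeks 12 and 24: recorded.
- Discussion: all adverse events recorded.

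The harms rule is incompatible with the Discussion as written, and with the visit and outcome sections on their natural reading.

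**2. What survives on any reading.** Serious adverse events, events leading to withdrawal, and mood through the Neuropsychiatric Inventory. Functional and quality-of-life scales are also collected. At risk are non-serious, non-mood events that do not cause withdrawal. Asthenia and sleep effects, which the harms section itself calls common, would often fall there.

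**3. The plan's own figure.** There is none for side effects. The available number of participants comes from Sample size {14}. With d = 2.1/3 = 0.7, a two-sided 5% paired t-test has exact power 89.4% at n = 23 and 90.7% at n = 24, so 24 is reproduced; 24/(1 − 0.20) = 30. These figures serve below only as the range of n.

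**4. Illustration of the loss.** Two inputs are assumptions, not in the documents: a share p = 5–30% of participants has a given side effect on levetiracetam (one event each), and a share s = 5–20% of those events is serious or causes withdrawal.

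- Recorded under the harms rule, n·p·s: from 24 × 0.05 × 0.05 = 0.06 to 30 × 0.30 × 0.20 = 1.8.
- Recorded in full, n·p: from 24 × 0.05 = 1.2 to 30 × 0.30 = 9.0.
- Chance of recording at least one under the rule, 1 − (1 − ps)^n: from 1 − 0.9975^24 = 6% to 1 − 0.94^30 = 84%.

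**5. How a zero count would read.** With full recording, no events among n participants gives a one-sided 95% upper bound of 1 − 0.05^(1/n): 11.7% for n = 24 and 9.5% for n = 30. Under the harms rule the same zero puts no such bound on non-serious events.

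**6. What full recording would buy.** Take the somnolence risk ratio of 1.51 from Table 1 as a working value, assume placebo risks of 5%, 10% and 20%, and treat periods as independent. An exact McNemar test at two-sided 5% then has power 0.3%, 2.1% and 6.6% with 24 participants, and 0.6%, 3.3% and 8.5% with 30. The gain is a usable description of harms by period, not a powered test.

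**The case against.** The strongest defence is that the harms section concerns safety records for regulatory purposes, while side effects are gathered separately as outcome data. The text does not draw that line. The rule says such events are not recorded within the study, rather than not reported onward, and the Discussion's promise is made for adverse events in the same terms. If this was the intention, the protocol has to say so. The case report form, the full protocol and the visit-schedule figure are not shown, so a suitable page may already exist; that reduces the cost of the fix but leaves the conflict in place.

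Several objections do stand. A reader might infer that non-serious events will certainly go unrecorded and that the side-effect objective therefore cannot be answered. The documents do not support that: other sections say these effects are recorded, serious events, withdrawals and mood are kept on any reading, and the secondary objective speaks of significant side effects. Nor can a count of lost reports be drawn from the documents. Table 1 does not grade seriousness, and its risk ratios come from an epilepsy meta-analysis at 1000–4000 mg/day that was not confined to adults.

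It is also fair that this concerns a secondary outcome of a pilot study, that the primary outcome and sample size are unaffected, and that the safety-only scenario in the addendum is conditional on prolonged restrictions.

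**Conclusion.** The point holds as an internal contradiction with a material consequence. The harms rule conflicts with Outcomes {12}, Subsequent visits and the Discussion, and the passages must be reconciled. If the rule is the one applied, the placebo comparison is largely unanswerable for non-serious, non-mood events that do not cause withdrawal, and sparse records could be misread as good tolerability.

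The contradiction rests on the text alone. Its size does not: the contrast of 0.06–1.8 recorded events with 1.2–9.0 depends on assumed rates and only indicates the scale. The direction does not depend on them, provided that some side effects are non-serious and tolerated.

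The make-up of Table 3 is a lesser, separate matter. Background and rationale {6a} and Table 1 give somnolence and fatigue or asthenia as main adverse events, whereas Table 3 leaves asthenia unsolicited and does not name somnolence. Its entry for effect on sleep may partly cover somnolence.

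**What to change.** - Remove the non-recording sentence from Adverse event reporting and harms {22}, and bring that section into line with Outcomes {12}, Subsequent visits and the Discussion.
- Record non-serious adverse events reported at the nine contacts after randomisation (weeks 2, 4, 8, 12, 14, 16, 20, 24 and 28) in the case report form with onset date, severity and treatment period. Screening and baseline precede dosing and belong to no treatment period. The week 28 call follows weaning, so events reported there should be placed by onset date.
- Compare the levetiracetam and placebo periods within participants, with estimates and intervals rather than reliance on tests. The exact method can be left to the analysis plan.
- As a secondary step, check Table 3 against Background and rationale {6a} and Table 1.

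The contacts already ask about side effects, so the added work is modest data entry and, if none exists, one form page. The trial is open and enrolled its first participant in December 2019, so a protocol amendment is needed. Data for participants already enrolled may be incomplete; the report should state from which date non-serious events were recorded.
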